### Tertiary Outcome Measure

#### Service Adherence and Satisfaction

Service adherence is measured by the number of modules accessed and the number of check-ins completed by the intervention participants. A total of 3 questionnaires assess service satisfaction. The first questionnaire assesses 3 main domains: enjoyment and ease of use, usefulness, and degree of comfort with service requirements. This questionnaire requires participants to rate whether they agree or disagree with 11 statements about the service, for example, *I enjoyed using Smooth Sailing*. The second questionnaire asks participants to report on 18 service use barriers across 3 key domains: technical, personal, or intervention-specific (answered yes or no), for example, *My internet connection didn’t work*. The third questionnaire examines participants’ use of the websites and CBT programs suggested by the service (answered yes, no, or I can’t remember). Participants are also asked to report if they have been contacted by the school counsellor during the study period and if they felt comfortable when this occurred. Participants are also asked to provide an overall rating of helpfulness of the service (answered on a Likert scale of 1 to 5 from extremely unhelpful to extremely helpful) and their suggestions for improvements or any other comments (2 free response options).

### Assessment of Safety

#### Data Monitoring

A data safety monitoring board is not utilized because the study targets a nonclinical population, blinding is not used, and the service provides a real-time monitoring and notification system of participants’ thoughts of death and self-harm. An Outcomes Advisory Group has been established to provide specific monitoring, governance, and reporting of adverse events and trial safety. This consists of the CI, chief scientist of the Black Dog Institute, a medical expert in child and adolescent psychiatry, and a clinical psychologist. This team meets monthly, and on an as-needed basis, to monitor the safety of the trial. During baseline, 6-week, and 12-week assessments, the research team notifies the Outcomes Advisory Group by email every fortnight of the total number of students participating and the notifications received for each school. This group is also responsible for responding to any complaints.

#### Harms

Throughout the study period, the duty of care for all students remains with their participating school. A trained mental health researcher from the Black Dog Institute is present at all school visits, alongside a school staff member. The school counsellor and a private breakout space is made available for any students who become distressed during the assessments. In the control condition, all students are provided with an information sheet of help-seeking resources and services at baseline, 6-week, and 12-week assessment. In the intervention condition, the Smooth Sailing service includes a question assessing thoughts of dying or harming oneself. This is part of the PHQ-9 screening measure for depression and aims to provide an objective measure of symptom severity if completed truthfully. However, further assessment from a trained mental health professional is required for the extent of an individual’s suicide risk to be fully determined. If a student reports the presence of these thoughts during the assessments, information about suicide support services is immediately provided by the service through a pop-up. The school counsellors are also notified using the Web-based portal and email system. The school counsellors are also notified when any participant in the intervention condition reports severe depression or anxiety symptoms, or there is risk of significant harm as identified by the school. The counsellors are notified to conduct the follow-up assessments to determine participants’ risk, using normal school protocols. A list of local services and resources is provided to the school counsellors to assist them in following up with students. The child and adolescent psychiatrist in the Outcomes Advisory Group is also available to provide advice and assistance to the school counsellors throughout the study period. School counsellors are asked to report on follow-ups to the research team via phone call or email with a record-keeping option on the school counsellor Web portal. The research team also inquire about adverse events at each of the school visits and report on these in their fortnightly reports to the Outcomes Advisory Group. At the final study visit, all students are provided with a list of mental health resources and services information.

### Data Handling, Storage, and Access

The study is hosted on the servers of the Black Dog Institute Research Platform, Faculty of Medicine, UNSW. These servers are encrypted with data backups occurring daily. This platform and its associated data are only accessible to authorized and approved personnel. When registering, participants create password-protected accounts and the platform allocates a unique identification number. For analyses, data are deidentified by removing names, email address, and mobile phone numbers. Students who actively withdraw will have their data removed and a withdrawal confirmation email will be sent from the research team. The platform retains data from the students who are lost to follow-up. All data will be stored securely for a minimum of 15 years.

### Auditing

Researchers follow step-by-step guidelines for each study visit to ensure consistency across different trial sites and research team members. A decision-making guide for trial conduct is provided to all research staff. School packages are mailed to schools ahead of time, which included trial documents, such as an explanatory paragraph for the school newsletter, an agenda for the baseline visit, and a list of local support services, to facilitate familiarity with the consent process and study procedure. Instructional documents for intervention school counsellors are provided to ensure adherence with the study protocol and to guide their use of the Web-based portal. All research staff debrief with the CI or research manager after each school visit. Fortnightly research team meetings are held to discuss and audit the conduct of the trial. The research team also have frequent contact with the school counsellors to assess any adverse events.

### Analysis

Data are collected using the Black Dog Institute electronic health platform. Data will be downloaded into Microsoft Excel and exported to SPSS Version 22.0 (SPSS Inc) for analysis. Primary analyses will be undertaken on an intention to treat basis, including all participants randomized, regardless of treatment received. Effectiveness of Smooth Sailing will be established by a change in the GHSQ scores between baseline and 12 weeks using a mixed-effects model repeated-measures analysis. The school will be included in analyses as a random effect to evaluate and accommodate clustering effects. In analyses of scaled secondary variables, methods comparable with those of the primary analysis will be used. An analysis of covariance will be conducted for the secondary outcomes of anxiety, depression, distress, functioning, mental health literacy, and barriers to help-seeking, controlling for baseline scores. To determine the effect of the intervention on help-seeking, 2 binary logistic regression analyses will be used. In model 1, the dependent variable will be help-seeking from adults at 12 weeks. The baseline result will be entered at step 1 in the model, with the study arm entered at step 2. In model 2, the dependent variable will be not seeking help at all at 12 weeks despite a need. The baseline result will be entered at step 1, with the study arm entered at step 2.

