### Randomization

Assignment of schools to the control or intervention condition is carried out according to the International Council for Harmonisation guidelines [32] and performed by a researcher not involved in the day-to-day conduct of the trial. Schools are allocated to a single condition (cluster design) to avoid contamination and for administrative convenience [33]. A minimization approach [34,35] is used to ensure balance across conditions in terms of the Index of Community Socio-Educational Advantage level (<1000 vs ≥1000), gender mix (coeducational vs single sex), and year level involved (year 9 students only vs multiple or other years). Minimization is undertaken in StataCorp LLC Stata statistical software version 14.2 using the rct_minim procedure [36]. The pool of already available schools is sorted in random order using the Excel 2003 data analysis random number generator and entered into the minimization routine in ascending order using the factors specified above. Subsequent schools are assigned to an intervention arm using rct_minim in the order that they join the trial and provide complete information. As this trial uses a no-treatment comparator control group, participants and researchers are not blinded to the allocation assignment.

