### Sample Size

The target sample size for this trial is 1600. This calculation is based on detecting an effect size of 0.20, which is similar to that obtained in previous school-based depression intervention research [9]. The statistical power level is set at 0.8, alpha=.05 (2-tailed), whereas a correlation of 0.5 is assumed between the scores at baseline and endpoint. A design effect is calculated assuming an intraclass correlation of 0.02 and an average school sample of 300 students to allow for possible clustering effects. This estimate was derived from previous Australian school–based studies [9]. The estimated sample size also accommodates for a 20% attrition rate based on previous school-based trials [43]. To achieve the desired sample size and ensure representation from a range of different types of schools, the target is set at 16 schools with approximately 100 students participating per school.

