**Primary outcome**					
	General Help-Seeking Questionnaire	Intentions to seek help	Yes	No	Yes

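### If the school random effect is fitted as a single intercept, it drops out of the primary baseline-to-12-week contrast and leaves that contrast without cluster adjustment

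*Protocol article*

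**What the plan says.** The Analysis section establishes effectiveness by "a change in the GHSQ scores between baseline and 12 weeks using a mixed-effects model repeated-measures analysis". On clustering it adds only: "The school will be included in analyses as a random effect to evaluate and accommodate clustering effects". It does not say whether this is an intercept, a school-by-time effect or a school effect on change, and it names no degrees-of-freedom method. Table 5 schedules the GHSQ at baseline and 12 weeks only, so the primary model has two waves.

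For the scaled secondary outcomes, the same section plans an analysis of covariance controlling for baseline.

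Under Randomization, "A minimization approach [34,35] is used to ensure balance across conditions in terms of the Index of Community Socio-Educational Advantage level", and also in terms of gender mix and year level. The Analysis section neither lists these factors as covariates nor rules them out.

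**The concern.** A reader takes the school term as the protection that a cluster-randomised comparison needs. In a two-wave model, a time-constant school intercept adds the same amount to a student's baseline and 12-week scores, so it vanishes from the difference. The between-arm comparison of change is then tested as if students, not schools, had been randomised. Any school-to-school variation in change goes into the estimate but not into its standard error.

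The primary result would look cluster-adjusted while carrying an interval that is too narrow and a false-positive rate above 5%. This also sits badly with the Sample Size section, which treats clustering as important enough to apply a design effect.

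**Working it through.** The plan states no standard error or interval for the primary model, so there is no figure of its own to reproduce on this point. The contrast examined is the between-arm difference in change, because the Objectives section compares the service with school-as-usual.

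**Inputs.**
- Intraclass correlation 0.02, baseline-endpoint correlation 0.5, 20% attrition, 16 schools of about 100 students (Sample Size). Retained per school: 100 × 0.8 = 80.
- 22 schools randomised, 10 intervention and 12 control (Results). Enrolment is not given. Assuming the target of 1600 was met, retained per school is 1600 × 0.8 / 22 ≈ 58.
- Correlation *c* of a school's effect between the two waves: not in the documents, taken as 0.5 to 1.

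**Step 1: cancellation.** Write a score as school effect + student effect + error. With a time-constant school effect *s*, the change is (*s* + …) − (*s* + …), and *s* disappears. Model fits confirm this. In one simulated trial (16 schools × 40 students, *c* = 0.5, intraclass correlation 0.02), school and student intercepts gave a standard error of 0.0795 for arm-by-time. That equals ordinary least squares on change scores ignoring school. A school effect on change gave 0.1094. At an intraclass correlation of 0.05 the figures were 0.0820, 0.0820 and 0.1780.

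**Step 2: variance left out.** In units of the outcome SD:
- total variance of change = 2(1 − 0.5) = 1;
- school variance of change = 2 × 0.02 × (1 − *c*);
- intraclass correlation of change = 0.04(1 − *c*).

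**Step 3: error rate.** With *m* retained per school, true SE / model SE = √[1 + (*m* − 1) × 0.04(1 − *c*)], and type I error = 2[1 − Φ(1.96 / ratio)]. Example with *m* = 80 and *c* = 0.8: 1 + 79 × 0.008 = 1.632; √1.632 = 1.277; 1.96 / 1.277 = 1.535; error 12.5%.

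| *c* | ICC of change | SE ratio, 16 × 80 | Type I error (simulated) | SE ratio, 22 × 58 | Type I error (simulated) |
|---|---|---|---|---|---|
| 1.0 | 0 | 1.00 | 5.0% (4.6%) | 1.00 | 5.0% (5.2%) |
| 0.9 | 0.004 | 1.15 | 8.8% (8.4%) | 1.11 | 7.7% (7.6%) |
| 0.8 | 0.008 | 1.28 | 12.5% (12.6%) | 1.21 | 10.4% (11.4%) |
| 0.5 | 0.020 | 1.61 | 22.2% (21.4%) | 1.46 | 18.0% (18.2%) |

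Simulations used 4,000 replicates per scenario. An analysis that carries school-level variance in change on cluster degrees of freedom rejected in 4.4% to 5.4% throughout. A baseline-adjusted analysis with school-level error rejected in 4.5% to 5.6%.

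**Step 4: minimisation factors.** Time-constant effects of these factors cancel from change just as the school intercept does; only factor-by-time effects matter. With one perfectly balanced factor left out (16 schools), type I error was 5.4%, 4.0% and 1.4% for factor-by-time effects of 0, 0.1 and 0.2 SD. Omission therefore errs on the conservative side.

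**The case against.** The strongest reply is that the article never says intercept-only. A school-by-time effect, or a school effect on change, fits the same sentence, and the stated aim of accommodating clustering favours such a reading. Under it nothing cancels, and a model that constrains baseline means to be equal across arms would cancel only in part. The article is condensed, and random-effects structure is often settled in an analysis plan that is not shown here. This stands as far as it goes: the defect belongs to one reading of the text, not to every reading. But that reading is the ordinary one, the article does commit to a change contrast with a single clustering term, and the permitted readings give different false-positive rates.

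Three stronger conclusions might be inferred, and the documents support none of them.
- That the primary interval is wrong outright. It is correct even with an intercept alone if *c* = 1, and the documents give no *c*.
- That error rates near a third are to be expected. These need *c* = 0, meaning school effects wholly redrawn within 12 weeks among the same students.
- That the minimisation factors are excluded and that this invalidates the interval. The article is silent on covariates, and omission errs in the opposite, conservative direction.

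It is also fair to say that changing a primary model after data collection in an unblinded trial is more than a wording edit.

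**Conclusion.** The point holds conditionally. With a school intercept alone, the stated term does not adjust the primary contrast for clustering, and type I error is nominal only if school effects are perfectly stable over 12 weeks. Modest instability (*c* of 0.9 to 0.8) gives about 9% to 12.5% with 16 schools and 8% to 10% with 22. At *c* = 0.5 the figures are about 22% and 18%.

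These rest on the protocol's own intraclass correlation and baseline-endpoint correlation, equal school sizes, an assumed range for *c* and, for 22 schools, an assumed total of 1600 enrolled. Perfect stability is hard to rely on here: the Control section lets control schools run whatever mental health activities they choose during the trial, so change can differ between schools even without an intervention effect. Whether the minimisation factors are covariates is a lesser matter of precision, not a threat to validity.

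**What to change.** State that the primary repeated-measures model includes a random school-by-time (school-on-change) effect, tested with small-sample, cluster-level degrees of freedom.

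Alternatively, model the 12-week GHSQ on arm and baseline GHSQ with a random school intercept and the same degrees of freedom. Baseline adjustment is already planned for the scaled secondary outcomes. It is also more precise than a correctly clustered change analysis. With 8 schools per arm, *m* = 80 and *c* = 0.5, the SE is √[(2/8)(0.015 + 0.735/80)] = 0.078, against √[(2/8)(0.020 + 0.98/80)] = 0.090 for change. This route needs a stated method for students without a 12-week score, so that the commitment to analyse all randomised participants is kept.

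As a secondary improvement, enter the three minimisation factors as fixed covariates, with their time interactions if the repeated-measures form is kept.

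The cost is a somewhat wider but correct interval and up to three between-school degrees of freedom: 20 to 17 with 22 schools (critical *t* 2.09 to 2.11), or 14 to 11 with 16. Because endpoint collection has finished and researchers are not blinded, the change should be dated and documented before the arm comparison is run.

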**Interventions provided**						
	Web-based psychoeducation	Yes	Yes	Yes	Yes	Yes
	Self-directed Web-based cognitive behavioral therapy	No	No	Yes	Yes	Yes
	Face-to-face sessions with a school counsellor to provide counselling and/or referral to external services	No	No	No	Yes	Yes

**Table 3 table3:** Module overviews.

Title	Content description
What is mental health?	Information about mental health issues that are common among youth and when it might be time to seek help
Feeling on edge	Information on anxiety, how to identify it, potential causes, where to seek help, and practical tips for managing it
Waves of sadness	Information on depression, differences between sadness and depression, potential causes, how and where to seek help, and practical tips to cope
When it’s time to tell someone	Information about when to seek help, how to talk to friends and parents, seek help from a general practitioner, and the roles of different health professionals
When a mate needs a hand	Ways to help others including having a private chat, seeking help together, respecting the treatment process, and the importance of looking after yourself
Don’t fret, help is here	Offers access to 2 evidence-based, free Web-based cognitive behavioral therapy programs, produced by Australian universities. Young people can select which program they prefer

In the Smooth Sailing service, school counsellor follow-up notifications are initiated if a student is allocated to Steps 3 or 4 or if a student reports having thoughts that they would be better off dead or thoughts of hurting themselves in the past 2 weeks (ie, score >0 on item 9 of the PHQ-9). School counsellors conduct the follow-up sessions during school time but after completion of the researcher visit. School counsellors follow their normal school protocols and duty of care procedures when attending to the notified students, initiating external referrals and parental contact when necessary.

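### If the school effect in the primary GHSQ model is a random intercept only, it cancels from the baseline-to-12-week contrast and leaves clustering in change unaccounted for

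*Protocol article*

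**What the plan says.** Schools are the unit of allocation (Randomization): "Schools are allocated to a single condition (cluster design) to avoid contamination and for administrative convenience".

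The primary test is described in Analysis: "Effectiveness of Smooth Sailing will be established by a change in the GHSQ scores between baseline and 12 weeks using a mixed-effects model repeated-measures analysis". Clustering is handled there by one sentence: "The school will be included in analyses as a random effect to evaluate and accommodate clustering effects". The section does not say whether the school effect is an intercept only, does not mention a school-by-time effect, and does not say whether the arms' baseline means are constrained to be equal.

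Table 5 schedules the GHSQ at baseline and 12 weeks but not at 6 weeks, so the repeated measures are a single pair per student.

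Sample Size expects clustering to matter: "A design effect is calculated assuming an intraclass correlation of 0.02". It also assumes a baseline-to-endpoint correlation of 0.5 and 20% attrition.

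For the scaled secondary outcomes, Analysis promises methods comparable with the primary analysis and then names an analysis of covariance controlling for baseline.

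**The concern.** Analysis names a clustering term and states its purpose. For the contrast named in the same paragraph, the ordinary form of that term does not serve the purpose.

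A school random intercept describes schools that are persistently higher or lower at both visits. A comparison of change removes such differences before the term can act. What remains is school-to-school variation in change, and an intercept does not represent it. Such variation is plausible here. Follow-up of notified students depends on local practice ("School counsellors follow their normal school protocols and duty of care procedures when attending to the notified students"), and control schools may run whatever mental health activities they choose. Neither fact shows how large the variation is.

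If it is present, the standard error is too small, the interval too narrow and the p-value too optimistic. The fault would be easy to miss, because the output would still list a school variance and look cluster-adjusted.

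**Working it through.** The plan gives no standard error or type I error for the primary contrast, so there is no figure to reproduce. Its design effect, 1 + (m − 1) × ICC, is 1 + 299 × 0.02 = 6.98 at its stated 300 students per school and 1 + 99 × 0.02 = 2.98 at its target of 100. Either way the plan expects clustering to raise the variance. (Whether 1600 follows from its inputs is a separate question.)

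**Inputs from the protocol:** ICC 0.02; student correlation 0.5; 20% attrition; 16 schools of about 100, hence 80 analysed; 22 schools randomized, 10 against 12.

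**Assumptions:** total variance 1 at each visit; the ICC of 0.02 applies at each visit; the 0.5 correlation applies to the within-school part (variance 0.98); 1600 enrolled across the 22 schools, hence 1600 × 0.8 / 22 ≈ 58 analysed per school; and c, the correlation between a school's effects at the two visits, which the documents do not give.

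**Step 1: the cancellation.** Write a student's score as fixed part + school intercept + student part. In 12-week minus baseline the school intercept vanishes. The variance of change is 2 × 0.98 × (1 − 0.5) = 0.98 per student, and the standard error with n per arm is √(0.98 × 2/n).
- 8 + 8 schools of 100: √(0.98 × 2/800) = 0.0495.
- 8 + 8 schools of 80: √(0.98 × 2/640) = 0.0553.

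Generalised least squares with a school intercept and free baseline means gives the same values (0.0495 and 0.0553) whether the school variance is 0, 0.02, 0.1 or 0.5. With 20% of 12-week scores missing from schools of 100 it is 0.0539 at all four. In three simulated datasets the fitted mixed-model z values equalled those of a student-level t-test on change: 0.518, 2.337 and 1.403.

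**Step 2: the variance that should be there.** If a school's effects at the two visits correlate c, its change has variance 2 × 0.02 × (1 − c) = 0.04(1 − c). The true variance of the contrast exceeds the one in Step 1 by

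VIF = 1 + m × 0.04(1 − c) / 0.98,

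and the actual size of a nominal 5% test is 2 × [1 − Φ(1.96/√VIF)].

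| c | VIF, m = 80 | Type I error, 16 schools of 80 | VIF, m = 58 | Type I error, 22 schools of 58 |
|---|---|---|---|---|
| 1.0 | 1.000 | 5.0% | 1.000 | 5.0% |
| 0.9 | 1.327 | 8.9% | 1.237 | 7.8% |
| 0.8 | 1.653 | 12.7% | 1.473 | 10.6% |
| 0.5 | 2.633 | 22.7% | 2.184 | 18.5% |

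Example, m = 80 and c = 0.5: VIF = 1 + 80 × 0.02/0.98 = 2.633, so the correct standard error is 0.0553 × √2.633 = 0.0898.

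**Step 3: simulation.** In 2000 null trials per setting with 16 schools of 80, the intercept-only test rejected 21.8% of the time at c = 0.5 and 13.4% at c = 0.8. A test on school-level mean changes stayed between 4.8% and 5.9%.

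**Step 4: equal baseline means imposed.** With schools of 100 and an intercept only, the standard error now depends on the school variance: 0.0429 at 0 and 0.0474 at 0.02. Cancellation is then partial. The term still does not represent school-specific change: splitting the 0.02 into 0.01 stable and 0.01 school-by-time gives 0.0747 under this parameterization, and 0.0863 with free baseline means.

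**The case against.** The strongest reply is that the defect is inferred. The text says only that school is a random effect. It does not say intercept-only and does not exclude a school-by-time effect, and an article may leave the covariance structure to the full analysis plan. Change could also be the outcome itself, with a random school effect, and then variation in change is carried directly. This stands: a reader might infer that the plan fixes an independent-students test, and the document does not support that. What remains is that Analysis names the term and its purpose, and that its most literal implementation fails that purpose.

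Second, the size of the error depends on a correlation found nowhere in the documents; if school means move together there is no inflation. This also stands. A reader might take the 18% to 23% figures as those implied by the plan's own ICC. Sample Size does not say that its 0.02 refers to change, so they are one end of an assumed range.

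Third, a reader might infer that the scaled secondary outcomes share the fault. Analysis names baseline-adjusted analysis of covariance for them and puts school as a random effect in the analyses generally. A school random effect does act on the arm contrast in that model. They are affected only if the repeated-measures form is used instead.

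**Conclusion.** The point holds conditionally. With a school random intercept and free baseline means, the primary arm-by-time test carries no between-school variation and equals a test on independent students' change. Under the stated assumptions the type I error is about 9%, 13% or 23% for 16 schools of 80, and 8%, 11% or 18% for 22 schools of 58, at between-visit school correlations of 0.9, 0.8 or 0.5. It is 5% at a correlation of 1. The 22-school figures also assume 1600 enrolled, which the protocol does not report. The algebra is exact; the range is illustrative. It deserves action because the literal reading puts the primary p-value at risk and a small change to the model removes that risk.

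**What to change.** For the primary outcome, specify one of the following:
- a random school-by-time effect in the repeated-measures model, kept even if its estimated variance is small; or
- a model of 12-week GHSQ adjusted for baseline GHSQ, with a random school intercept.

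These are different models with different precision, so choose one and name it. In either, test the arm effect on between-school degrees of freedom (22 − 2 = 20 for the schools randomized, before any further school-level covariates). For the scaled secondary outcomes, confirm that the analysis of covariance includes the school random effect.

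The cost is one line of model specification and somewhat wider intervals. If schools do change differently, those are the correct intervals. If the sponsor already intends one of these models, stating it costs nothing.

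### The two secondary help-seeking-behaviour models are listed without a school term in a school-randomised trial; if school is left out, the 5% test could run at about 18% to 22%

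*Protocol article*

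**What the plan says.** The Randomization section of the protocol article allocates whole schools to one arm. The Analysis section then proceeds in this order:

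- **Primary outcome (GHSQ):** a mixed-effects repeated-measures model, followed by the sentence "The school will be included in analyses as a random effect to evaluate and accommodate clustering effects".
- **Scaled secondary outcomes:** "In analyses of scaled secondary variables, methods comparable with those of the primary analysis will be used". The next sentence reads "An analysis of covariance will be conducted for the secondary outcomes of anxiety, depression, distress, functioning", and goes on to mental health literacy and barriers, with adjustment for baseline.
- **Binary secondary outcomes:** "To determine the effect of the intervention on help-seeking, 2 binary logistic regression analyses will be used". Model 1 is for help-seeking from adults at 12 weeks. Model 2 is for not seeking help at 12 weeks despite a need. In both, the baseline result goes in at step 1 and study arm at step 2.

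No school term, random intercept, GEE or cluster-robust error is named for the two binary models.

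**The concern.** When schools are randomised, students in the same school tend to respond alike, and the arm effect is estimated from a small number of schools. A logistic regression with only baseline response and arm treats every student as independent. Its standard error for arm is too small, its interval too narrow and its p-value too optimistic.

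The article does not leave this model to another document. It names the procedure, the outcome, the terms and the order of entry, and the randomised unit is not among the terms. An analyst following the text literally would fit an ordinary logistic regression. At stake are the confidence intervals and tests for help-seeking behaviour, which stands next to intentions in the stated aims. A false positive there could be reported as evidence that the service changes what students do.

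There is a smaller gap of the same kind for the scaled outcomes. One sentence promises methods comparable with the primary model and the next names an analysis of covariance, without saying whether school stays in it.

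**Working it through.** **No stated figure to reproduce.** The article gives no error rate for the logistic models. The benchmark is the nominal level in Sample Size: "The statistical power level is set at 0.8, alpha=.05 (2-tailed").

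**Inputs**

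- Intraclass correlation (ICC) 0.02, from Sample Size: "A design effect is calculated assuming an intraclass correlation of 0.02 and an average school sample of 300 students". It was set for the sample-size calculation; no ICC is given for either binary outcome. Using it here is an assumption.
- 16 schools of about 100 students with 20% attrition (Sample Size): 100 × 0.8 = 80 analysed per school.
- 22 schools randomised, 10 and 12 (Results). The article gives no enrolled number. Spreading the target evenly gives 1600 × 0.8 / 22 = 1280 / 22 ≈ 58 analysed per school. This is also an assumption.
- The 300 students per school in the design-effect sentence is not used, because it disagrees with the planned 100 per school. That mismatch is a separate matter and does not decide this point.

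**Formulas**

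- Design effect: DE = 1 + (m − 1) × ICC, where m is the number analysed per school.
- A test that ignores schools understates the standard error by a factor √DE, so its true two-sided type I error is 2 × [1 − Φ(1.96 / √DE)].
- Its interval is 1/√DE of the width it should have.

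**At ICC 0.02**

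- m = 80: DE = 1 + 79 × 0.02 = 2.58; 1.96 / 1.606 = 1.220; type I error 22.2%; interval 62% of the proper width.
- m = 58: DE = 1 + 57 × 0.02 = 2.14; 1.96 / 1.463 = 1.340; type I error 18.0%; interval 68% of the proper width.

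**Sensitivity to the ICC**

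| ICC | m = 58: DE, type I error | m = 80: DE, type I error |
|---|---|---|
| 0.005 | 1.285, 8.4% | 1.395, 9.7% |
| 0.01 | 1.57, 11.8% | 1.79, 14.3% |
| 0.02 | 2.14, 18.0% | 2.58, 22.2% |
| 0.04 | 3.28, 27.9% | 4.16, 33.7% |

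**Simulation check.** Beta-binomial data with no arm effect and an assumed event rate of 30% were tested with an unadjusted log-odds-ratio test that ignores schools, 4,000 runs per setting. At ICC 0.02 the rejection rate was 23.1% for 8 + 8 schools of 80 and 16.8% for 10 + 12 schools of 58. With an event rate of 15% and 8 + 8 schools of 80 it was 21.5%. With ICC 0 it was 5.1%, so the excess comes from the clustering. A t-test on school proportions in the same simulated data rejected 4.6% to 5.3% of the time across the settings run.

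**The case against.** The strongest reply is that the school random-effect sentence speaks of analyses in the plural, is not limited to the GHSQ, and comes before every secondary method. Listing the baseline response and arm as entered predictors does not exclude a random intercept. A reader might infer that the protocol commits to single-level logistic regression and that the error rate will be about 20%. The documents do not support that as fact: nowhere does the article say clustering is ignored, and the general sentence can be read to cover these models. What remains is a mismatch. The carry-over sentence is confined to scaled variables, and the two models are written out term by term without school.

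The size is also conditional. The 0.02 was not given for these outcomes, and the 58 per school is derived from the target. Both the formula and the simulation leave out the baseline response, and the three school-level minimisation factors were not modelled. Either could reduce the between-school variation that matters. The lower rows of the ICC table give some idea of that: even at 0.005 the error is 8% to 10%, not 5%.

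Two further criticisms are tempting and fail. A reader might infer that the analysis of covariance contradicts the commitment to include everyone randomised. That sentence is about the primary analyses, so a secondary analysis does not breach it. A reader might also object that a 12-week analysis of covariance ignores the 6-week scores. The secondary hypothesis is a 12-week contrast, so using the 6-week scores would be a choice about efficiency and not a correction.

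**Conclusion.** The point holds as a specification fault in two secondary models. As listed, they contain no school term although schools were randomised. If the general random-effect sentence is meant to apply, the listed models need to be brought into line with it.

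If school is left out, the true type I error of the nominal 5% test is about 18% to 22%, assuming ICC 0.02 and 58 to 80 students analysed per school, and about 8% to 34% for ICC 0.005 to 0.04. These figures describe what follows from omitting school; they do not predict what the analysts will do.

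The GHSQ analysis has its own mixed model with the school effect and is untouched, so the primary conclusion is not at risk. Because the affected outcomes are secondary, this is a correction that should be made rather than one that endangers the trial's main result. For the scaled outcomes the text needs only a clarification that the analysis of covariance keeps the school effect.

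**What to change.** Specify both binary models as mixed-effects logistic regression, with the baseline response and arm as fixed effects and a random school intercept. GEE clustered on school is an acceptable alternative. In either case name a small-sample correction, since there are only about 22 schools.

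State that the analysis of covariance for the scaled secondary outcomes includes the school random effect, so that it agrees with the sentence before it.

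The change is to the analysis wording only and needs no new data. Its cost is wider intervals for help-seeking behaviour: at ICC 0.02, by a factor of about √2.14 = 1.46 to √2.58 = 1.61 compared with a model that leaves school out, before any small-sample correction.
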